## 2. Methods

### 2.1. Study Design, Setting, and Timeline

The study is a controlled, randomized, non-profit parallel group superiority clinical trial fulfilling the CONSORT criteria for non-pharmacological treatment. See Figure 2. The estimated time for the entire duration of the study is 13 months as summarized in the Gantt Chart. See Table 1.

A total of 30 patients will be allocated to either CBT-E or CBT-VR. We opted for 15 patients for each group. Based on a sample of 100 healthcare workers of our University Hospital suffering from Adjustment Disorders and treated with CBT at our center (pre-treatment CGI score = 3.95 ± 0.74 and post-treatment CGI score = 2.39 ± 1.07, unpublished data), to point out a difference between the 2 treatment groups (CBT-E and CBT-VR) of at least 1 point at the CGI, the estimated sample size should be at least 26, with 13 patients in the CBT-E group and 13 patients in the CBT-VR group (by considering confidence interval = 95%, statistical power = 90%, ratio of sample size of 1). 

Participants will be assessed at baseline, during each session of CBT, and at the end of the training. Recruitment will be carried out at the outpatient care setting of INAIL, the Italian National Institute for Insurance against Accidents at Work, a public entity safeguarding workers against physical injuries and occupational diseases. The randomized clinical trial will then be conducted at the Center for Work-Related Stress and Occupational Mental Disorders of a major University Hospital in central Italy (Azienda Ospedaliero-Universitaria Pisana, AOUP). The Center includes a multidisciplinary team comprising occupational physicians, psychiatrists, and psychologists. A Trial Management Team (TMT) will be formed to conduct the day-to-day management of the trial. This will include the chief investigator, trial physicians with different roles, and the data manager. The group will meet at least once per week to discuss issues related to the progress of the trial and to ensure the trial is running well.

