### 2.2. Eligibility Criteria, Tools, and Informed Consent

Recruited subjects will be workers with a diagnosis of AD or PTSD determined by means of the presence of items corresponding to DSM-5 criteria for the disorders. Inclusion and exclusion criteria for randomization in the arms of the study are summarized in Table 2. A case report form will be fulfilled for each participant reporting personal data at the beginning of the training and physiological and clinical data at baseline (T0), at every CBT session, and at the end of the training (T1). Personal background, physiological, and clinical data are summarized in Table 3.

Regarding informed consent, a first information sheet will be handed out at the outpatient clinic of INAIL during the recruitment phase. Subsequently, trial assessors of the Center for Work-Related Stress and Occupational Mental Disorders will discuss the trial, with referred patients considering the information provided in the information sheet. The assessors will then obtain written consent from patients willing to participate in the trial.

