### 2.6. Data Collection, Management, Statistical Method, and Ethical Considerations

The collection of the data will be performed in paper and later entered electronically. All data will be confidential. Enrolled patients will be registered in anonymous form using an identification code (progressive number), which will be used for data management solely for research purposes. The recorded data will be anonymized to avoid any link with patients. The data will be archived in an Excel program and kept at the trial sites under the responsibility of the principal investigator. Access to the data will be allowed only to personnel directly involved in the research protocol and protected by a password. Patients will not be identified by name in future publications. Participants will be informed about all main aspects of the research and of their right to refuse to take part or to withdraw consent to participation at any moment. An insurance policy to protect the subjects participating in the trial will be stipulated with the insurance company selected by the University of Pisa.

The data will be recorded in a specifically designed database and elaborated by means of the SPSS software (version 26). The Kolmogorov–Smirnov test will be used to examine variables for normal (Gaussian) distribution. Therefore, the comparisons between patients’ groups for variables of non-Gaussian distribution will be performed by means of non-parametric statistical tests; in particular, the Mann–Whitney test for independent samples will be used. The Student’s t-test for independent samples will be used to compare groups for variables of Gaussian distribution. According to non-Gaussian or Gaussian distribution of paired data, the Wilcoxon test and the Friedman test or the Student’s t-test for dependent samples and the repeated measures ANOVA will be used, respectively. The chi-square test will be used to compare the frequencies of categorical variables. Correlations between continuous variables will be examined by means of Spearman’s coefficient in case of non-Gaussian distribution or by means of Pearson’s coefficient in case of Gaussian distribution. A regression analysis will be used to explore the relationship between more variables. A *p* value less than 0.05 will be considered significant.

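### Thirteen patients per group does not give 90% power for a 1-point CGI difference at the only post-treatment SD stated (1.07): power is about 63% at 13 and 70% at the planned 15 per group

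*Protocol article*

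**What the plan says.** Section 2.1 describes a parallel-group superiority trial with 30 patients, 15 per arm. The sizing rests on 100 healthcare workers with Adjustment Disorder treated with CBT at the same centre: "pre-treatment CGI score = 3.95 ± 0.74 and post-treatment CGI score = 2.39 ± 1.07, unpublished data". The aim of the calculation is "to point out a difference between the 2 treatment groups (CBT-E and CBT-VR) of at least 1 point at the CGI", with the settings "by considering confidence interval = 95%, statistical power = 90%, ratio of sample size of 1". The result is "the estimated sample size should be at least 26, with 13 patients in the CBT-E group and 13 patients in the CBT-VR group".

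The section does not say which of the two SDs was used, whether the 1-point difference is in end-of-treatment scores or in change from baseline, or what pre-post correlation was assumed.

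Section 2.6 compares groups by the independent-samples t-test, or by Mann-Whitney if the variable is not Gaussian; a p "value less than 0.05 will be considered significant". The CGI listed in section 2.3 and Table 3 is the CGI-I, which the clinician rates relative to the patient's state at baseline. Section 2.2 widens the population beyond the planning sample: "Recruited subjects will be workers with a diagnosis of AD or PTSD".

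**The concern.** Randomised arms are expected to be alike before treatment, so a 1-point difference between them can arise only afterwards. The SD that matters for comparing end scores is therefore the post-treatment one, and the article's own data show the spread growing from 0.74 to 1.07. Sample size varies with the square of the SD, so this choice roughly doubles the requirement: (1.07/0.74)² = 2.09.

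This is the article's only justification of the sample size. If the stated power is too high, a null result would be read as strong evidence against a 1-point advantage of VR. In fact about 3 in 10 true effects of that size would be missed at 15 per arm (1 − 0.695 = 0.305).

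**Working it through.** **Inputs.** From section 2.1: difference 1 point; SD 0.74 before and 1.07 after treatment; power 90%; ratio 1; 13 per group calculated and 15 planned. From sections 2.1 and 2.6: 95% confidence and p < 0.05, taken as two-sided 5% because sidedness is not stated. Test: independent-samples t-test (section 2.6). Discontinuations are replaced (section 2.5), so no dropout inflation is applied.

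**Formulas.** Normal approximation: n per group = 2 × (1.960 + 1.282)² × SD² / difference², where the squared sum is 10.507. Exact t-test: noncentral t with 2n − 2 degrees of freedom and noncentrality = difference / (SD × √(2/n)).

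**1. Reproducing the article's 13.** With SD 0.74, the normal approximation gives 2 × 10.507 × 0.5476 = 11.5, so 12 per group. The t-test gives 88.5% power at 12 and 91.1% at 13, so 13 is the smallest sufficient number. The figure reproduces with the pre-treatment SD.

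**2. The same calculation with the post-treatment SD.** 2 × 10.507 × 1.1449 = 24.06, so 25 per group. The t-test gives 89.9% at 25 and 91.1% at 26, so 26 per group, 52 in total.

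**3. Power at the article's numbers, SD 1.07.**

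| Per group | Noncentrality | Power, t-test | Power, normal approx. |
|---|---|---|---|
| 13 | 2.38 | 62.8% | 66.4% |
| 15 | 2.56 | 69.5% | 72.6% |

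At 15 per group the difference detectable with 90% power is 1.31 points. The 95% CI half-width is 2.048 × 1.07 × √(2/15) = 0.80 point.

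**4. Other routes to 13.**
- Omitting the factor 2 for two arms: 10.507 × 1.1449 = 12.03, rounded up to 13.
- Reading 26 per group as a total and halving it.
- A change score, with SD = √(0.74² + 1.07² − 2 × r × 0.74 × 1.07). This reaches 90% at 13 per arm if r is about 0.71.

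**5. Sensitivity to the comparison (t-test, two-sided unless noted).** The correlations are assumptions; the article gives none.

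| Reading | SD | 13 per arm | 15 per arm |
|---|---|---|---|
| End score, SD 1.07 | 1.07 | 63% | 70% |
| Same, one-sided 5% | 1.07 | 75% | 80% |
| Root mean square of the two SDs | 0.92 | 76% | 82% |
| Change score, r = 0.3 | 1.10 | 60% | 67% |
| Change score, r = 0.5 | 0.95 | 73% | 80% |
| Change score, r = 0.7 | 0.76 | 89% | 93% |
| Baseline-adjusted, r = 0.5 (SD = 1.07 × √(1 − r²)) | 0.93 | 75% | 81% |

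For a change score at the planned 15 per arm, 90% power needs r of about 0.65.

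**The case against.** The strongest reply is that a change-score comparison may have been meant. Section 2.1 gives both pre and post values, section 2.5 lists variations in the parameters among the outcomes, and section 2.6 lists repeated measures ANOVA. With r of about 0.71 at 13 per arm, or 0.65 at 15, the 90% would stand. This is possible, so a reader should not infer that the true power is 63% or 70%: those figures are conditional on an end-score comparison with SD 1.07. But the article states no correlation and does not tie the sample size to such an analysis. The CGI-I it lists is already a rating of change, with no baseline score to subtract or adjust for. The planning data, with scores before and after treatment, may not even be on the CGI-I. That weakens 1.07 as the trial's SD, but it weakens 0.74 equally.

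A reader might also infer that the pre-treatment SD was certainly used by mistake. The documents do not support that, because several routes lead to 13.

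Nor do they support the inference that 1.07 is probably too small because the trial adds PTSD and other occupations. No SD for PTSD is given, and the exclusion of other Axis I diagnoses and the drug-free or stable-therapy criterion in Table 2 could narrow the spread.

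Finally, 15 rather than 13 per arm are planned, and the Discussion calls VR superiority a secondary outcome. The larger number helps, but only to about 70% with SD 1.07. Section 2.1 still sizes the trial on the between-arm difference.

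**Conclusion.** The concern holds in a limited form. The article's inputs and its result do not agree for an end-of-treatment comparison: with SD 1.07, two-sided 5% and the t-test of section 2.6, 90% power needs 26 per group, and the article's total of 26 equals the number needed in each arm. The stated 90% exceeds the computed power by about 27 percentage points at 13 per group (90 − 62.8) and about 20 at 15 (90 − 69.5).

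This rests on three assumptions: the 1-point difference is in end scores, testing is two-sided, and SD 1.07 from the Adjustment Disorder series carries over to the trial. Averaging the SDs, one-sided testing or a change score with r up to 0.5 still leaves 13 per arm short of 90%. Only a fairly high pre-post correlation would reach it, and the article gives none.

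**What to change.** In section 2.1:

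1. State which CGI version the planning data and the trial use, whether the comparison is of end scores or of change, and which SD entered the calculation.
2. Delete the statement that 13 per group gives 90% power.
3. Report that, with SD 1.07 and a two-sided 5% t-test, 15 per arm gives about 70% power for a 1-point difference, a detectable difference of 1.31 points at 90% power and a 95% CI half-width of about 0.80 point. Say that the SD comes from an Adjustment Disorder sample.
4. Claim a higher power for a change-score or baseline-adjusted comparison (for example 80% or 81% at an assumed r = 0.5, 15 per arm) only if a baseline CGI severity score is collected, that analysis is specified, and the correlation is taken from the 100-worker data. The CGI-I alone cannot support it.

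The cost is one reworded paragraph and, for step 4, one correlation from data the sponsor already holds plus a baseline severity rating. No extra patients are required; the stated power becomes less favourable.

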### 2.2. Eligibility Criteria, Tools, and Informed Consent

Recruited subjects will be workers with a diagnosis of AD or PTSD determined by means of the presence of items corresponding to DSM-5 criteria for the disorders. Inclusion and exclusion criteria for randomization in the arms of the study are summarized in Table 2. A case report form will be fulfilled for each participant reporting personal data at the beginning of the training and physiological and clinical data at baseline (T0), at every CBT session, and at the end of the training (T1). Personal background, physiological, and clinical data are summarized in Table 3.

Regarding informed consent, a first information sheet will be handed out at the outpatient clinic of INAIL during the recruitment phase. Subsequently, trial assessors of the Center for Work-Related Stress and Occupational Mental Disorders will discuss the trial, with referred patients considering the information provided in the information sheet. The assessors will then obtain written consent from patients willing to participate in the trial.

### 2.3. Measures

The whole sample will be investigated by means of the BDI-II, SAS, JCQ, PSQI, PDI, DTS, and CGI-I.

The BDI-II consists of 21 groups of statements and is one of the most widely used psychometric tests for measuring the severity of depression. This questionnaire presents statements that describes the way the patient has been feeling (quotes about sadness, pessimisms, loss of pleasure, guilty feelings [..]) during the past two weeks. Answers are scored on a scale value of 0 to 3. A total score of 0–13 is considered minimal range, 14–19 is mild, 20–28 is moderate, and 29–63 is severe, e.g., 0, I do not feel sad; 1, I feel sad much of the time; 2, I am sad all the time; 3, I am so sad or unhappy that I can’t stand it. The Italian version of the BDI-II was administered to a sample of 723 college students and to a sample of 72 depressed patients. Alpha and test-retest reliabilities were computed along with associations with age and education. The BDI-II proved a reliable and valid measure of depressive symptoms in the Italian context [19].

The SAS is a 20-item self-report assessment device built to measure anxiety levels based on scoring in 4 groups of manifestations: cognitive, autonomic, motor, and central nervous system symptoms. Answering the statements, a person should indicate how much each statement applies to him or her within a period of one or two weeks prior to taking the test. Each question (“I feel tense, nervous, restless, or agitated”) is scored on a Likert-type scale of 1–4 (based on these replies: “a little of the time,” “some of the time,” “good part of the time,” “most of the time”). Some questions are negatively worded to avoid the problem of set response. The overall assessment is based on the total score. The total raw scores range from 20 to 80. The raw score then needs to be converted to an “Anxiety Index” score using the chart on the paper version of the test. The “Anxiety Index” score can then be used to determine the clinical interpretation of one’s level of anxiety: 20–44, Normal Range; 45–59, Mild to Moderate Anxiety Levels; 60–74, Marked to Severe Anxiety Levels; 75 and above, Extreme Anxiety Levels (e.g., 0, I do not feel sad; 1, I feel sad; 2, I am sad all the time and I can’t snap out of it; 3, I am so sad and unhappy that I can’t stand it). This tool has been translated and validated in many languages, including Italian. The internal consistency reliability coefficient was 80 [36].

The JCQ is a self-administered workplace environment questionnaire designed to measure social and psychological characteristics of jobs. It consists of 49 items that explore the domains of decision latitude, psychological demands, physical demands, job insecurity, and social support. The response set is designed to assess the validity of the statement about the work environment on a Likert-type scale ranging from 1 to 4 (1 = not at all, 2 = not, 3 = yes, 3 = extremely yes). Each task statement should tell what action is performed; for whom or what you do this action; what is produced by this action; and which equipment, tools, materials, work aids, and processes you use when performing this action. (e.g., How often do you perform this task? 1, Regularly—on a daily/weekly basis; 2, Periodically—on a monthly basis; 3, Infrequently—on a yearly basis). The results are used to measure the high-demand/low-control/low-support model of job strain development. Authorized translations of the full JCQ instrument from English, which have been specifically approved and which are available from the JCQ Center, are French-Canadian, French-Belgium, Flemish-Belgium, Spanish, Swedish, Dutch, Italian, and Japanese [9].

The PSQI is a 19 items questionnaire that measures several different aspects of sleep, offering seven component scores and one composite score. The component scores consist of subjective sleep quality, sleep latency (i.e., how long it takes to fall asleep), sleep duration, habitual sleep efficiency (i.e., the percentage of time in bed that one is asleep), sleep disturbances, the use of sleeping medication, and daytime dysfunction. Each item is weighted on a 0–3 interval scale. In scoring the PSQI, seven component scores are derived, each scored from 0 (no difficulty) to 3 (severe difficulty). The component scores are summed to produce a global score (range: 0–21). Higher scores indicate worse sleep quality (e.g., 0, Very good; 1, Fairly good; 2, Fairly bad; 3 Very bad). The Italian version of the questionnaire provides a good and reliable differentiation between normal and pathological groups, with higher scores reported by people characterized by impaired objectively evaluated sleep quality [37,38].

The PDI is a self-report instrument developed to retrospectively measure the distress experienced by the subject at the time of the potentially traumatizing event or immediately after. It is composed of 13 items, each scored on a 5-point Likert-type scale ranging from 0 to 4 (0 = not at all, 1 = slightly, 2 = somewhat, 3 = very, and 4 = extremely true), with the total score ranging from 0 to 52, and higher scores indicating increased distress. Statements explore cognitive response to the trauma (e.g., I thought I might die), emotional distress (e.g., I was horrified by what happened) or physical symptoms (e.g., I had physical reactions like sweating, shaking, and pounding heart). The PDI demonstrates good test–retest reliability, convergent and divergent validity, and good internal consistency. The internal consistency of the PDI was satisfactory with a Cronbach’s alpha of 0.87. The reliability, validity, internal consistency, and the temporal stability of the Italian version of the PDI resulted to be good, falling within the range of those reported in the original validation study [39].

The DTS is a self-report instrument developed to assess DSM PTSD symptoms. It is a 5-point Likert-type scale, self-report instrument that assesses the DSM symptoms of PTSD. It is composed of 17 items, each scored on a 5-point Likert-type scale evaluating frequency (0 = “not at all” to 4 = “every day”) and severity (0 = “not at all distressing” to 4 = “extremely distressing”) of the most disturbing trauma (e.g., of statements: Have you had painful images, memories, or thoughts of the event?). Respondents rate how much trouble they have had with each symptom. The scale demonstrated good test–retest reliability (r = 0·86), internal consistency (r = 0·99). The Italian version of the tool by Pieraccini et al. (1999) has been approved by the original authors [13,40].

The clinical global impression-improvement scale (CGI-I) is a 7-point scale that requires the clinician to assess how much the patient’s illness has improved or worsened relative to a baseline state at the beginning of the intervention. (e.g., clinicians ask: “Compared to the patient’s condition at baseline, this patient’s [average] condition has...?” and rate as: Very much improved; Much improved; Minimally improved; No change; Minimally worse; Much worse; Very much worse). The Italian version of the tool has been approved by the National Institute of Mental Health [41].

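### Section 2.1 sizes the trial on a CGI score with pre- and post-treatment values, but the only CGI form listed for collection is the change-rated CGI-I, so the stated power is unsupported for the recorded scale

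*Protocol article*

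**What the plan says.** **Sizing (Protocol article, section 2.1).** The planning data come from 100 healthcare workers with Adjustment Disorder treated with CBT at the centre: "pre-treatment CGI score = 3.95 ± 0.74 and post-treatment CGI score = 2.39 ± 1.07, unpublished data". The target is "to point out a difference between the 2 treatment groups (CBT-E and CBT-VR) of at least 1 point at the CGI", giving at least 26 patients, 13 per arm, "by considering confidence interval = 95%, statistical power = 90%, ratio of sample size of 1". The planned size is slightly larger: "A total of 30 patients will be allocated to either CBT-E or CBT-VR", 15 per arm. The paragraph speaks of the CGI without naming a subscale. It is the only power statement in the article.

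**Instruments (section 2.3 and Table 3).** "The whole sample will be investigated by means of the BDI-II, SAS, JCQ, PSQI, PDI, DTS, and CGI-I". Table 3 also lists CGI-I and no other CGI form. Section 2.3 defines it as a 7-point clinician rating of how far the illness "has improved or worsened relative to a baseline state at the beginning of the intervention", running from very much improved, through no change, to very much worse.

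**Timing (section 2.2).** The case report form holds "physiological and clinical data at baseline (T0), at every CBT session, and at the end of the training (T1"). The text does not say which instruments are rated at which visit.

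**The concern.** The scale behind the planning values was scored before treatment, with a mean and a spread, and again afterwards. A rating of change from the start of treatment cannot behave like that: before treatment every patient is at no change by definition, so there is no baseline SD to report. The 3.95 ± 0.74 therefore does not fit the CGI-I as section 2.3 describes it, and no other CGI form is listed for collection.

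At stake is the only power statement in the article. One point on a severity score and one point on a change rating are different quantities, and their SDs need not agree. If the sizing used one form and the trial records the other, the 26 patients and the 90% power do not carry over to the data that will exist at the end. The timing matters as well: a baseline clinician rating not taken before the first session cannot be recovered later by an analysis plan.

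**Working it through.** **Inputs.** Difference between arms 1 point; power 90%; allocation 1:1; SDs 0.74 (pre) and 1.07 (post); 15 per arm planned (all section 2.1). A two-sided 5% level is my reading of the 95% confidence interval given there.

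**Formulas.** Normal approximation: n per arm = 2 × SD² × (1.960 + 1.282)² / 1². Exact power: two-sample t test with noncentrality 1 / (SD × √(2/n)) and 2n − 2 degrees of freedom.

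**1. Reproducing the stated 26.**

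| SD used | n per arm, normal | n per arm, t | Matches 13 per arm? |
|---|---|---|---|
| 0.74 (pre-treatment) | 2 × 0.5476 × 10.51 = 11.5, so 12 | 13 (power 91%; 12 gives 89%) | Yes |
| 0.92 (root mean square of the two) | 18 | 19 | No |
| 1.07 (post-treatment) | 2 × 1.1449 × 10.51 = 24.1, so 25 | 26 | No |

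One-sided tests with these three SDs do not give 13 either (10 to 21 per arm). A change-score SD, √(0.74² + 1.07² − 2r × 0.74 × 1.07), gives 13 per arm only for a pre-post correlation r of about 0.68 to 0.72. No correlation is stated, and this route also needs a pre-treatment score. Every route found to the stated figure thus uses the pre-treatment value, which the CGI-I as defined cannot supply.

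**2. What 15 per arm buys on the CGI-I.** No SD is identified for this scale, so the SDs below are assumed and only show the range (difference 1 point, two-sided 5%, t test at T1).

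| Assumed CGI-I SD | Noncentrality, n = 15 | Power, n = 15 | n per arm for 90%, t |
|---|---|---|---|
| 0.8 | 3.42 | 91% | 15 |
| 1.0 | 2.74 | 75% | 23 |
| 1.2 | 2.28 | 60% | 32 |
| 1.4 | 1.96 | 47% | 43 |

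**3. What 15 per arm buys on the scored CGI at T1.** The relevant SD is then that of the outcome, 1.07. Unadjusted, the noncentrality is 1 / (1.07 × √(2/15)) = 2.56, and power is 70% (73% by the normal approximation). Adjusted for T0, the residual SD is 1.07 × √(1 − r²), with 27 degrees of freedom:

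| Assumed r (T0 with T1) | Residual SD | Power, n = 15 |
|---|---|---|
| 0.5 | 0.927 | 81% |
| 0.65 | 0.813 | 90% |
| 0.7 | 0.764 | 93% |

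The r values are assumptions. These figures do not measure the mismatch itself; they show what the claim in section 2.1 would become if the scored form were added and tested at the end of treatment.

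**The case against.** Four points can be made for the plan.

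- **The comparison can still be made.** Section 2.1 targets a difference between arms, and that needs no baseline. CGI-I is collected and can be compared at T1 with the t test or Mann–Whitney test of section 2.6. This stands. A reader might infer that the sized endpoint is never measured or cannot be analysed; the documents do not support that. What lacks support is the planning SD, and with it the power.
- **Severity is not stated.** Section 2.1 names no subscale. If the seven anchors in section 2.3 were numbered 1 to 7, no change would be 4, close to the pre-treatment mean of 3.95. If the centre really scored CGI-I in this way, 1.07 would be a CGI-I SD. A pre-treatment SD of 0.74 speaks against it, since a change rating should not vary before any change has occurred. Severity is thus the likelier reading, but it remains an inference, and the first request must be to say which form was used. Even on the CGI-I reading, an SD of 1.07 would not give 13 per arm.
- **No paired test is assigned to the CGI-I.** It is tempting to say that the plan tests CGI-I from T0 to T1. Section 2.6 lists paired tests in general and section 2.2 speaks of clinical data in general; neither assigns CGI-I to T0 or to a paired comparison. That charge is not made here.
- **A fuller protocol or analysis plan may settle it.** It could name the form. But the sizing paragraph and the instrument list do not fit each other as published, so this is more than omitted detail.

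**Conclusion.** The point holds as an inconsistency between the sizing paragraph and the instrument list. The planning values in section 2.1 appear to come from a scored CGI, probably severity, that is not listed for collection, and the 90% power is unsupported for the CGI-I that is.

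The size of the shortfall is unknown. The trial may be adequately powered on CGI-I or well short of it, and the document cannot say which. Listing the scored form would not by itself rescue the 90%: the stated 26 matches the pre-treatment SD, while the outcome at T1 has the larger SD. These conclusions rest on a two-sided 5% test, on normal-theory power for an ordinal 7-point scale, and on SDs and correlations marked above as assumed.

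**What to change.** 1. In section 2.1, state which CGI form the 3.95 and 2.39 refer to, and which SD produced the 26.
2. If it is a severity score, add that rating at T0 and T1 to section 2.3 and Table 3, name it as the sized endpoint, compare arms on the T1 score adjusted for T0, and restate the power with the outcome SD and a justified correlation. If no correlation near 0.65 or above can be defended, either the number of patients or the power claim has to change. CGI-I can stay as a further outcome at T1.
3. If CGI-I is kept as the sized endpoint, say that it is analysed at T1 only, and restate section 2.1 with a CGI-I SD and its source.

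The cost is one more case report form item at T0 and T1, rated by the clinician who already rates CGI-I, and a rewording of sections 2.1 and 2.3 and Table 3. The T0 item has to be in place before the first patient starts treatment. Any larger sample would follow from the restated power and would be the only substantial cost.
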